### Hypotheses

#### Primary hypothesis

Kava will be superior to placebo in the treatment of GAD symptoms, assessed by change in Structured Interview Guide for the Hamilton Anxiety Rating Scale (SIGH-A) [38] scores after the 16-week treatment phase.

#### Secondary hypotheses

2)Kava will be superior to placebo on a range of secondary affective disorder outcome scales (Beck Anxiety Inventory [39], Penn State Worry Questionnaire [40]*,* and Montgomery–Åsberg Depression Rating Scale [41]).3)Kava will be superior to placebo on health-related quality of life measured using The World Health Organization Quality of Life - BREF (WHOQOL-BREF) [42], the Social Re-adjustment Rating Scale [43], and the Kessler Psychological Distress Scale [44].4)Overall sexual satisfaction and performance rated on the Arizona Sexual Experiences Scale [45] will be in favour of kava compared to placebo, in women but not men.5)Personality trait factors including anxiety, extraversion, socialization, and aggression rated on the Swedish Universities Scales of Personalities (SSP) may be associated with GAD symptomatology and will be measured via this self-reporting measure.6)Anterior cingulate cortex (ACC) activation and metabolite profiles will be differentially affected in the kava treatment group over placebo from baseline to week 8. Specifically, for ACC metabolite levels, there will be an increase in GABA and decrease in glutamate/glutamine ratio (Glu/Gln); ACC activation: reduction in activation during resting state; ACC activation: reduction in activation associated with anticipatory anxiety in a task-dependent manner. Further, individual differences in rostral ACC activation measured pre-treatment may predict GAD treatment outcomes for kava compared to placebo. Increased levels of activity in the ACC will also be associated with better clinical outcome in GAD participants.7)Response to kava will be moderated by GABA transporter polymorphisms. Specifically, for every rs2601126-T allele or rs2697153-A allele an individual carries, the greater the reduction of anxiety that will be observed.8)Individuals in the kava group will have distinct gene expression change profiles compared to the placebo group. Specifically, we hypothesise that expression of GABA pathway genes will be up-regulated following kava treatment and remain stable in the placebo group.

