**Fig. 3 Fig3:**
[figure not shown]
Clinical trial flowchart

Participants will be required to attend seven visits at the study sites at week 0 (baseline), 2, 4, 8, 12, 16, and 18. At the baseline visit, participants will complete informed consent forms, screening assessments, and mood and anxiety questionnaires (self-reporting and interview-based). Brain imaging component visits (Melbourne site only) are to be scheduled within one week of baseline and week 8 visits.

The study employs an additional two-week single-blind placebo-controlled post-study observation period (that is, for a total trial length of 18 weeks - refer Fig. 3).

All eligible participants will be randomly allocated to a treatment arm, and corresponding treatment will be provided following clearance of blood tests taken at the baseline visit. All subsequent visits will follow the same outline of the baseline session excluding consent forms and screening assessments and including a safety assessment. In addition, participants will be required to provide a blood sample within several days of the baseline, and at week 2, 8, and 16 visits. For female participants not taking hormone-modulating contraception who are otherwise eligible to partake in the brain imaging components, the baseline visit is to be scheduled on days 1–5 of the menstrual cycle.

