### Secondary outcome measures

In addition, the Beck Anxiety Inventory (BAI) will be used as a participant self-report scale to assess anxiety levels. It consists of 21 items ranging from 0 (not present) to 3 (severe). These items are more somatically orientated than the SIGH-A and provide additional information on anxiety outcomes.The Penn State Worry Questionnaire (PSWQ) is a 16-item self-report measure of the intensity and excessiveness of worry. Examples of items are “Many situations make me worry” and “Once I start worrying, I cannot stop.” Participants rate items on a 5-point Likert scale from 1 (“Not at all typical of me”) to 5 (“Very typical of me”). Total scores range from 16 to 80, with higher scores indicating pathological worry. The PSWQ is widely used and has shown good to very good internal consistency, test-retest reliability, and discriminant validity for GAD versus other anxiety disorders [49].Mood will be assessed at each visit using the SIGMA (Structured Interview Guide for the Montgomery–Åsberg Depression Rating Scale (MADRS)), a diagnostic questionnaire which measures severity of depression symptoms. The SIGMA provides structured questions for each item to ensure standardisation of administration. Each item yields a score of 0 to 6, producing an overall score ranging between 0–60. A higher MADRS score indicates more severe depression. Inter-rater reliability with the SIGMA is reported to be excellent (*r* = 0.93) [50]. The use of this scale is important, as sufferers of GAD often have co-morbid depression, which may affect their response to treatment.Quality of life/life stressor measures will be administered at selected visits. The WHOQOL-BREF measure is a reduced version of the original instrument, designed for clinical trial use. It comprises 26 items, covering the domains of physical health, psychological health, social relationships, and environment. The Social Readjustment Rating Scale (SRRS) is a scale using ‘Life Change Units’ (LCUs) to quantify the number and severity of life stressors occurring in the preceding 12-month period. Both will be administered at baseline and at week 16. The Kessler Psychological Distress Scale (K10) is a 10-item questionnaire designed to obtain a global measure of perceived stress level, with questions pertaining to anxiety and depressive symptoms experienced in the past four-week period. For this study it will be administered at each visit.The Arizona Sexual Experiences Scale (ASEX) will be employed to assess the effects of kava on participants’ sexual functioning. Specifically, the self-report scale explores effects on desire, arousal level, and physiological responses over the course of the past week. It consists of five self-report items, each rated on a 6-point scale. Total scores can range between 5–30, where higher scores indicate greater sexual dysfunction. The use of this scale is important, as conventional SSRI antidepressant treatments (used to treat GAD) commonly cause sexual side effects, and results of a previous study [37] showed a significant improvement in sex drive for women. If this finding is replicated, it will show a point of difference between kava and conventional treatments. Due to the sensitive nature of the items, completion of this scale is optional.The Swedish Universities Scales of Personalities (SSP) is a 91-item self-rated questionnaire based on the Karolinska Scales of Personality (KSP), a scale designed to measure stable personality traits related to psychopathology [51]. It assesses four general temperament dimensions: anxiety, extraversion, socialization, and aggression. This questionnaire will be given to participants after their initial baseline visit to complete in their own time and return at the next visit.Genotyping of candidate and haplotype-tagging single nucleotide polymorphisms in monoamine, glutaminergic, and GABA transporter genes, measured via blood sample at week 1, will be achieved using a Sequenom Mass-Array.A custom RT^2^ PCR Array (Qiagen) will be used to examine gene expression of candidate genes (Table 1) at weeks 1 and 8.

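### Hypothesis 3 uses a 12-month life-event count (SRRS) as a superiority measure of quality of life, and 69% of its week-16 window precedes randomisation

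*Protocol article*

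**What the plan says.** The hypothesis under Secondary hypotheses, item 3, reads: "Kava will be superior to placebo on health-related quality of life measured using The World Health Organization Quality of Life - BREF (WHOQOL-BREF", followed by "the Social Re-adjustment Rating Scale [43], and the Kessler Psychological Distress Scale [44". One construct, one direction and three instruments are therefore fixed together. No instrument is singled out to carry the hypothesis.

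Under Secondary outcome measures, the SRRS is said to use life change units "to quantify the number and severity of life stressors occurring in the preceding 12-month period". Of the WHOQOL-BREF and the SRRS the same section says "Both will be administered at baseline and at week 16". No shorter look-back, such as events since the last assessment, is given for week 16. The paragraph introduces these instruments under a joint label that sets quality of life and life stressors side by side, so the article itself distinguishes the two.

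Treatment lasts 16 weeks (Treatment interventions, randomisation, and blinding). It starts only once the baseline blood tests are cleared (Study design and plan). Under Statistical analyses, every test of a treatment effect is two-sided at 0.05.

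**The concern.** Two features of the SRRS, as the article describes it, do not fit the role that hypothesis 3 gives it.

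- **Construct.** A score that adds up life events and their weight measures what happened to a person. Read literally, hypothesis 3 predicts fewer or less serious life events on kava than on placebo, and the article offers no rationale for that.
- **Window.** A 12-month look-back at week 16 is mostly a look at time before randomisation, and that time was already recorded at baseline.

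At stake is how one secondary result is read. A null SRRS comparison could be taken as evidence against a quality-of-life benefit when the scale had little chance of showing one. A significant one could be reported as better quality of life when it shows a difference in reported events. The primary outcome, the sample size and the safety assessments are not affected.

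**Working it through.** **Inputs from the protocol article**
- SRRS look-back: 12 months, taken as 52 weeks (Secondary outcome measures).
- SRRS assessments: baseline (week 0) and week 16 (same section).
- Arm size: 105 (Power analysis).
- Two-sided alpha: 0.05 (Statistical analyses).

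The article gives no power or effect size for the SRRS, so there is no stated figure to reproduce. Its sample-size calculation concerns SIGH-A only.

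**Step 1: the two windows**
- Baseline window: week −52 to week 0.
- Week-16 window: 16 − 52 = −36, so week −36 to week 16.
- Before randomisation: 36/52 = 69.2%. After randomisation: 16/52 = 30.8%.
- Overlap with the baseline window: week −36 to week 0, which is 36 of 52 weeks.
- If blood-test clearance delays treatment by one week (an assumption; the article gives no length), the untreated share is 37/52 = 71.2%.

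These are shares of time. They are shares of events only if events occur evenly over time.

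**Step 2: what the dilution could do (illustration only)**

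Suppose kava did change the life-event score over the 16 weeks, by a standardised effect d of 0.3, 0.4 or 0.5. These values are assumptions. Power with n = 105 per arm is approximately Φ(d√(n/2) − 1.96).

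| Score compared | Effect detected | Power at d = 0.3 / 0.4 / 0.5 |
|---|---|---|
| Events in the 16 weeks only | d | 58 / 83 / 95% |
| 52-week score, weeks independent | d√(16/52) = 0.555d | 23 / 36 / 52% |
| 52-week score, SD grows in proportion to the window | d × 16/52 = 0.308d | 10 / 14 / 20% |
| Change from baseline, weeks independent | d/√2 = 0.707d | 34 / 54 / 73% |

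Example, second row, d = 0.3: 0.3 × 0.555 = 0.166; 0.166 × √52.5 = 1.206; Φ(1.206 − 1.96) = 23%.

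In the last row the 36 shared weeks cancel. That leaves 16 treated weeks minus the 16 earliest weeks of the baseline window, hence the factor √2. It assumes that participants recall the shared weeks identically on both occasions.

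**Step 3: the other two instruments**
- WHOQOL-BREF: no look-back is stated, so no overlap can be shown.
- K10: the look-back is four weeks and the visits are "seven visits at the study sites at week 0 (baseline), 2, 4, 8, 12, 16, and 18". The pre-randomisation share at week w is max(0, 4 − w)/4, which is 50% at week 2 and 0% at weeks 4, 8, 12 and 16. At week 18, 2/4 = 50% of the window falls after the 16-week treatment phase.

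**The case against.** The strongest reply has three parts.

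**The SRRS is insensitive, not inert.** Sixteen of the 52 weeks follow randomisation, and less anxious people might plausibly meet, or report, fewer stressors. The pre-randomisation weeks are balanced between arms in expectation and, with consistent recall, cancel in a change score. This stands. A reader might infer that the scale cannot respond to treatment, or that the comparison is biased; the article supports neither. The reply does not rescue the construct, because a real effect on life events would still not be an effect on quality of life.

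**Two of the three instruments are sound.** A reader might conclude that hypothesis 3 cannot be answered at all. That goes too far. Nothing here touches the WHOQOL-BREF, and the K10 windows at weeks 4 to 16 lie after baseline, apart from any short delay before treatment starts. Nor does any rule require all three instruments to succeed.

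**The K10 schedule is not an error.** The K10 covers symptoms "experienced in the past four-week period. For this study it will be administered at each visit", so a reader might object that half the week-2 window is untreated time and half the week-18 window is still on treatment. The arithmetic is right, but nothing in the article makes either visit the K10 test. The averaging over the whole study under Statistical analyses is stated for SIGH-A only. Which visits enter a secondary comparison is commonly left to a statistical analysis plan, and none is shown here.

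It can also be said that the fault is only loose wording in one secondary hypothesis. It is indeed confined to that, but the wording fixes a direction and an instrument for a test of superiority.

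**Conclusion.** The point holds for the SRRS alone. Hypothesis 3 makes it a superiority measure of health-related quality of life, whereas the article's own description makes it a measure of exposure to stressors. At week 16, 69% of its window precedes randomisation and repeats what baseline already covered; 31% can reflect treatment. The harm is dilution and misreading of the result, not bias.

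The 69% rests on the stated look-back and visit times, with 12 months taken as 52 weeks, and does not depend on the illustrative power figures. Those rest on assumed effects and on assumptions about how weekly events vary; they show direction, not size. This is a secondary-outcome matter that should be corrected but does not threaten the trial's main conclusion.

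**What to change.** Remove the SRRS from the superiority measures in hypothesis 3 and let the WHOQOL-BREF and K10 carry it. Use the baseline SRRS score as a covariate or moderator of response. Only the baseline score suits that role, because the week-16 score includes time after randomisation. Report the week-16 SRRS descriptively by arm. If a statistical analysis plan exists, make the same change there.

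The change is to wording only: the SRRS is still collected at baseline and week 16, and the sample size is unaffected. The small cost is the loss of one secondary comparison.

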## Methods/Design

### Study design and plan

The design of the study is a phase III, multi-site, two-arm, 18-week, randomised, double-blind, placebo-controlled trial using a standardised pharmaceutical-grade, water-soluble extract of kava (240 mg of kavalactones per day) or matching placebo (inert plant-based fibre) in 210 currently anxious participants with GAD. The trial sites are at the Centre for Human Psychopharmacology (Swinburne University of Technology), Hawthorn, Melbourne, Australia and the Academic Discipline of Psychiatry (The University of Queensland) based at the Royal Brisbane and Women’s Hospital, Herston, Brisbane, Australia. Recruitment is scheduled to commence September 2015 and through to June 2017 (Fig. 2).

**Fig. 2 Fig2:**
[figure not shown]
Kava studies timeline summary

**Fig. 3 Fig3:**
[figure not shown]
Clinical trial flowchart

Participants will be required to attend seven visits at the study sites at week 0 (baseline), 2, 4, 8, 12, 16, and 18. At the baseline visit, participants will complete informed consent forms, screening assessments, and mood and anxiety questionnaires (self-reporting and interview-based). Brain imaging component visits (Melbourne site only) are to be scheduled within one week of baseline and week 8 visits.

The study employs an additional two-week single-blind placebo-controlled post-study observation period (that is, for a total trial length of 18 weeks - refer Fig. 3).

All eligible participants will be randomly allocated to a treatment arm, and corresponding treatment will be provided following clearance of blood tests taken at the baseline visit. All subsequent visits will follow the same outline of the baseline session excluding consent forms and screening assessments and including a safety assessment. In addition, participants will be required to provide a blood sample within several days of the baseline, and at week 2, 8, and 16 visits. For female participants not taking hormone-modulating contraception who are otherwise eligible to partake in the brain imaging components, the baseline visit is to be scheduled on days 1–5 of the menstrual cycle.

### Ethics and trial registry

This study has ethical clearance (Alfred Hospital Research Ethics Committee 137/14, University of Queensland Research Ethics Committee 2014000876, Swinburne University Human Research Ethics Committee 2014/204), and is registered on ClinicalTrials.gov (protocol number: NCT02219880).

### Recruitment

Participants will be recruited through various advertisement sources:A dedicated study websiteAdvertisements in local newspapers and radioA press release which may involve featured articles in newspapers and appearances by the chief investigator on radio and TVOnline advertisements, including the Swinburne University ‘Participate in Research’ webpage (http://www.swinburne.edu.au/lss/chp/projects/kava.html) and the websites of local anxiety disorder organisations (for example, Anxiety Disorders Association of Victoria, Anxiety Recovery Centre Victoria), Google, and FacebookPosters and brochures displayed on campus and in the waiting rooms of local Healthscope pathology centres and medical clinics

### Primary outcome measure

The primary outcome is symptoms of GAD measured by the Structured Interview Guide for the Hamilton Anxiety Rating Scale (SIGH-A), at baseline and subsequent visits up to 18 weeks following randomization. The SIGH-A is a widely used measure of anxious symptomatology in GAD research. It includes measures of persistent worry, anxiety, mood, and somatic symptoms. The SIGH-A has been used in previous studies of pharmacological and psychological treatments for people with GAD. It is reliable (intraclass correlation coefficients for inter-rater reliability of 0.98 and test-retest reliability of 0.88), has high convergent validity with structured clinical ratings of symptoms of GAD (for example, MINI PLUS 6.0 [46]), and is sensitive to change [47, 48].

### Secondary outcome measures

In addition, the Beck Anxiety Inventory (BAI) will be used as a participant self-report scale to assess anxiety levels. It consists of 21 items ranging from 0 (not present) to 3 (severe). These items are more somatically orientated than the SIGH-A and provide additional information on anxiety outcomes.The Penn State Worry Questionnaire (PSWQ) is a 16-item self-report measure of the intensity and excessiveness of worry. Examples of items are “Many situations make me worry” and “Once I start worrying, I cannot stop.” Participants rate items on a 5-point Likert scale from 1 (“Not at all typical of me”) to 5 (“Very typical of me”). Total scores range from 16 to 80, with higher scores indicating pathological worry. The PSWQ is widely used and has shown good to very good internal consistency, test-retest reliability, and discriminant validity for GAD versus other anxiety disorders [49].Mood will be assessed at each visit using the SIGMA (Structured Interview Guide for the Montgomery–Åsberg Depression Rating Scale (MADRS)), a diagnostic questionnaire which measures severity of depression symptoms. The SIGMA provides structured questions for each item to ensure standardisation of administration. Each item yields a score of 0 to 6, producing an overall score ranging between 0–60. A higher MADRS score indicates more severe depression. Inter-rater reliability with the SIGMA is reported to be excellent (*r* = 0.93) [50]. The use of this scale is important, as sufferers of GAD often have co-morbid depression, which may affect their response to treatment.Quality of life/life stressor measures will be administered at selected visits. The WHOQOL-BREF measure is a reduced version of the original instrument, designed for clinical trial use. It comprises 26 items, covering the domains of physical health, psychological health, social relationships, and environment. The Social Readjustment Rating Scale (SRRS) is a scale using ‘Life Change Units’ (LCUs) to quantify the number and severity of life stressors occurring in the preceding 12-month period. Both will be administered at baseline and at week 16. The Kessler Psychological Distress Scale (K10) is a 10-item questionnaire designed to obtain a global measure of perceived stress level, with questions pertaining to anxiety and depressive symptoms experienced in the past four-week period. For this study it will be administered at each visit.The Arizona Sexual Experiences Scale (ASEX) will be employed to assess the effects of kava on participants’ sexual functioning. Specifically, the self-report scale explores effects on desire, arousal level, and physiological responses over the course of the past week. It consists of five self-report items, each rated on a 6-point scale. Total scores can range between 5–30, where higher scores indicate greater sexual dysfunction. The use of this scale is important, as conventional SSRI antidepressant treatments (used to treat GAD) commonly cause sexual side effects, and results of a previous study [37] showed a significant improvement in sex drive for women. If this finding is replicated, it will show a point of difference between kava and conventional treatments. Due to the sensitive nature of the items, completion of this scale is optional.The Swedish Universities Scales of Personalities (SSP) is a 91-item self-rated questionnaire based on the Karolinska Scales of Personality (KSP), a scale designed to measure stable personality traits related to psychopathology [51]. It assesses four general temperament dimensions: anxiety, extraversion, socialization, and aggression. This questionnaire will be given to participants after their initial baseline visit to complete in their own time and return at the next visit.Genotyping of candidate and haplotype-tagging single nucleotide polymorphisms in monoamine, glutaminergic, and GABA transporter genes, measured via blood sample at week 1, will be achieved using a Sequenom Mass-Array.A custom RT^2^ PCR Array (Qiagen) will be used to examine gene expression of candidate genes (Table 1) at weeks 1 and 8.

**Table 1 Tab1:** Gene expression list

Gene symbol	Gene name
GABBR1	GABA, B receptor 1
GABBR2	GABA, B receptor 2
GABRA1	GABA, A receptor, alpha 1
GABRA2	GABA, A receptor, alpha 2
GABRA4	GABA, A receptor, alpha 4
GABRA5	GABA, A receptor, alpha 5
GABRA6	GABA, A receptor, alpha 6
GABRB1	GABA, A receptor, beta 1
GABRB3	GABA, A receptor, beta 3
GABRD	GABA, A receptor, delta
GABRE	GABA, A receptor, epsilon
GABRG1	GABA, A receptor, gamma 1
GABRG2	GABA, A receptor, gamma 2
GABRG3	GABA, A receptor, gamma 3
GABRQ	GABA, A receptor, theta
GABRR1	GABA, A receptor, rho 1
GABRR2	GABA, A receptor, rho 2
ADCY7	Adenylate cyclase 7
ADORA1	Adenosine A1 receptor
ADORA2A	Adenosine A2a receptor
CACNA1A	Calcium channel, voltage-dependent, P/Q type, alpha 1A subunit
CACNA1B	Calcium channel, voltage-dependent, N type, alpha 1B subunit
GNAI1	G protein, alpha inhibiting activity polypeptide 1
GNAQ	G protein, q polypeptide
GPHN	Gephyrin
SNCA	Synuclein, alpha
NSF	N-ethylmaleimide-sensitive factor
P2RX7	Purinergic receptor P2X, ligand-gated ion channel, 7
SLC1A3	Glial high affinity glutamate transporter
SLC32A1	Solute carrier family 32 (GABA vesicular transporter), member 1
SLC38A1	Solute carrier family 38, member 1
SLC6A1	Solute carrier family 6 (neurotransmitter transporter), member 1
SLC6A11	Solute carrier family 6 (neurotransmitter transporter), member 11
SLC6A12	Solute carrier family 6 (neurotransmitter transporter), member 12
SLC6A13	Solute carrier family 6 (neurotransmitter transporter), member 13
ABAT	4-aminobutyrate aminotransferase
ALDH5A1	Aldehyde dehydrogenase 5 family, member A1
GAD1	Glutamate decarboxylase 1
GLS	Glutaminase
GLUL	Glutamate-ammonia ligase
PHGDH	Phosphoglycerate dehydrogenase
DRD1	Dopamine receptor D1
DRD2	Dopamine receptor D2
DRD3	Dopamine receptor D3
DRD4	Dopamine receptor D4
DRD5	Dopamine receptor D5
COMT	Catechol-O-methyltransferase
DBH	Dopamine beta-hydroxylase
DDC	Dopa decarboxylase
MAOA	Monoamine oxidase A
TH	Tyrosine hydroxylase
SLC6A3	Solute carrier family 6 (dopamine transporter), member 3
SLC6A4	Solute carrier family 6 (serotonin transporter), member 4
MAOB	Monoamine oxidase B
HTR1A	Serotonin receptor 1A
GRIA1	Glutamate receptor, ionotropic, AMPA 1
GRIA2	Glutamate receptor, ionotropic, AMPA 2
GRIA3	Glutamate receptor, ionotropic, AMPA 3
GRIA4	Glutamate receptor, ionotropic, AMPA 4
GRIK1	Glutamate receptor, ionotropic, kainate 1
GRIK2	Glutamate receptor, ionotropic, kainate 2
GRIK4	Glutamate receptor, ionotropic, kainate 4
GRIK5	Glutamate receptor, ionotropic, kainate 5
GRIN1	Glutamate receptor, ionotropic, N-methyl D-aspartate 1
GRIN2A	Glutamate receptor, ionotropic, N-methyl D-aspartate 2A
GRIN2B	Glutamate receptor, ionotropic, N-methyl D-aspartate 2B
GRIN2C	Glutamate receptor, ionotropic, N-methyl D-aspartate 2C
GRM1	Glutamate receptor, metabotropic 1
GRM2	Glutamate receptor, metabotropic 2
GRM3	Glutamate receptor, metabotropic 3
GRM4	Glutamate receptor, metabotropic 4
GRM5	Glutamate receptor, metabotropic 5
GRM6	Glutamate receptor, metabotropic 6
GRM7	Glutamate receptor, metabotropic 7
GRM8	Glutamate receptor, metabotropic 8
ADRA1A	Adrenoceptor alpha 1A
ADRA1D	Adrenoceptor alpha 1D
ADRA2A	Adrenoceptor alpha 2A
ADRB2	Adrenoceptor beta 2
ADRB3	Adrenoceptor beta 3
SLC18A2	Vesicular monoamine transporter
SLC6A2	Norepinephrine transporter
CYP3A4	Cytochrome P450 3A4
CYP2D6	Cytochrome P450 2D6
CYP2E1	Cytochrome P450 2E1
AR	Androgen receptor
NRG1	Neuregulin-1
BDNF	Brain-derived neurotrophic factor
ABCG2	Breast cancer resistance protein
ABCB1	P-glycoprotein
GAPDH	Reference genes
SADH	Reference genes
B2M	Reference genesAnterior cingulate cortical (ACC) region metabolite profiles, including N-acetyl-l-aspartate (NAA), creatine (Crn), glutamate/glutamine (Glu/Gln), and gamma-amino butyric acid (GABA), will be measured using single voxel magnetic resonance spectroscopy (MRS) at weeks 1 and 8.ACC region activity at rest and functional connectivity network (that is, default mode network) will be analysed using resting-state functional magnetic resonance imaging (fMRI) at weeks 1 and 8.ACC region task-dependent activation levels associated with anticipatory anxiety will be assessed using task fMRI (the International Affective Picture System (IAPS; [52]) at weeks 1 and 8.Acute anxiety levels related to undergoing scanner session at weeks 1 and 8 will be measured on the Spielberger State-Trait Anxiety Inventory — Trait and State components [53].

Inclusion criteria*Aged between 18–70 yearsMeets the DSM-IV and DSM-5 diagnostic criteria for generalised anxiety disorder (GAD) based on structured interview; Mini International Neuropsychiatric Interview-6.0 (MINI 6.0) [54], (note that while the MINI 6.0 uses the DSM-IV criteria, the same criteria are used in the DSM-5)Presents with anxiety (SIGH-A ≥ 18) at the time of study entryFluent in spoken and written EnglishProvides a signed copy of the consent form

**MRI component* – Participant eligibility for the imaging component of the study will follow a listing of restrictions typical of imaging safety at the 3-T scanner. All participants will be right-handed, with no metallic implants, piercings, or residue. For females in the imaging component, there will be conditions of enrolment relating to menstrual cycle dates, and they must not be taking hormone-modulating contraception (such as oral contraceptive pills or hormonal implants).

Exclusion criteriaPrimary diagnosis other than GAD as determined by the MINI 6.0Presentation of moderate to severe depressive symptoms (MADRS ≥ 18) at time of study entryPresentation of suicidal ideation (≥3 on MADRS suicidal thoughts domain) at time of study entryCurrent diagnosis of a psychotic disorder (for example, schizophrenia) or bipolar I on structured interview (MINI 6.0)Current substance/alcohol use disorder on structured interview (MINI 6.0)Currently taking an antidepressant, mood stabiliser, antipsychotic, anticonvulsant, warfarin or thyroxin, or regularly using a benzodiazepine or opioid-based analgesic (more than two days per week)Current use of St John’s wort or contraindicated herbal medicationPrevious intolerance to kavaThree or more failed trials of pharmacotherapy for the current GAD episode Recently commenced psychotherapy (within four weeks of study entry) Known or suspected clinically unstable systemic medical disorder Diagnosed hepato-biliary disease/inflammation Elevated liver enzymes at baseline blood test Pregnancy or breastfeeding, or trying to conceive Not using a medically approved form of contraception (including abstinence) if female and of childbearing age Unable to participate in all scheduled visits, treatment plan, tests, and other trial procedures according to the protocol.

